## **Appendix 2. The Confusion Assessment Method Instrument (CAM)**

---

### The Confusion Assessment Method Instrument

---

#### Acute onset

1. Is there evidence of an acute change in mental status from the patient's baseline?

#### Inattention\*

2. A. Did the patient have difficulty focusing attention, for example, being easily distractible, or having difficulty keeping track of what was being said?

Not present at any time during interview.

Present at some time during interview, but in mild form.

Present at some time during interview, in marked form.

Uncertain.

B. (If present or abnormal) Did this behavior fluctuate during the interview, that is, tend to come and go or increase and decrease in severity?

Yes.

No.

Uncertain

Not applicable.

C. (If present or abnormal) Please describe this behavior:

#### Disorganized thinking

3. Was the patient's thinking disorganized or incoherent, such as rambling or irrelevant conversation, unclear or illogical flow of ideas, or unpredictable switching from subject to subject?

#### Altered level of consciousness

4. Overall, how would you rate this patient's level of consciousness?

Alert (normal).

Vigilant (hyper-alert, overly sensitive to environmental stimuli, startled very easily).

Lethargic (drowsy, easily aroused).

Stupor (difficult to arouse).

---

Coma (unarousable).

Uncertain.

#### Disorientation

5. Was the patient disoriented at any time during the interview, such as thinking that he or she was somewhere other than the hospital, using the wrong bed, or misjudging the time of day?

#### Memory impairment

6. Did the patient demonstrate any memory problems during the interview, such as inability to remember events in the hospital or difficulty remembering instructions?

#### Perceptual disturbances

7. Did the patient have any evidence of perceptual disturbances, for example, hallucinations, illusions, or misinterpretations (such as thinking something was moving when it was not)?

#### Psychomotor agitation

8. Part 1.

At any time during the interview, did the patient have an unusually increased level of motor activity, such as restlessness, picking at bedclothes, tapping fingers, or making frequent sudden changes of position?

#### Psychomotor retardation

8. Part 2.

At any time during the interview, did the patient have an unusually decreased level of motor activity, such as sluggishness, staring into space, staying in one position for a long time, or moving very slowly?

#### Altered sleep-wake cycle

9. Did the patient have evidence of disturbance of the sleep-wake cycle, such as excessive daytime sleepiness with insomnia at night?

---

\* The questions listed under this topic were repeated for each topic where applicable.

---

### Appendix 3. The Numeric Rating Scale (NRS)

[figure not shown]

---

**Appendix 4. The Fatigue, Resistance, Ambulation, Illness and Loss of Weight Index (FRAIL)**

**FRAIL SCALE**

|                |                                                                             |                                                                |
|----------------|-----------------------------------------------------------------------------|----------------------------------------------------------------|
| Fatigue        | Are you fatigued?                                                           | All/most of the time = 1
Some/a little/none of the time = 0 |
| Resistance     | Do you have difficulty walking up one flight of stairs without assistance?  | Yes = 1/No = 0                                                 |
| Ambulatory     | Do you have difficulty walking 1 block without assistance?                  | Yes = 1/No = 0                                                 |
| Illness        | Do you have more than 5 illnesses (confirm with doctor or medical records)? | Yes = 1/No = 0                                                 |
| Loss of Weight | Have you lost more than 5% of your weight in the past year?                 | Yes = 1/No = 0                                                 |

Scoring: robust (score = 0), prefrail (score = 1–2), and frail (score = 3–5)

---

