## G. Statistical Analysis

Data analysis will perform in September 2023. The Kolmogorov-Smirnov test is used to assess normality, independent sample t-test is used if normally distributed data, and Mann-Whitney U test is used otherwise for non-normally distributed data. Continuous variables with normal distribution are represented by mean and standard deviation (SD), and variables with non-normal distribution are represented by median and interquartile range (IQR). Categorical variables are expressed as frequencies and proportions and analyzed using chi-square tests or Fisher exact tests.

Primary outcome is compared between the two groups using chi-square test or Fisher exact test, with differences between groups expressed as relative risk (RR) and 95% confidence interval (CI). The linear mixed-effects model is used to compare the secondary outcomes, with baseline (T0) values as covariates, treatment, time, and the interaction of time and treatment as fixed effects, and the subject's random intercept as a random effect to account for differences in time. The treatment-by-time interaction term is tested first. If significant, between- and within-treatment differences are tested for each time

---

point, and analyses are adjusted for multiple comparisons using the Bonferroni test for differences in within-treatment anxiety scores from baseline (T0). Otherwise, the main effect of treatment was tested next, and no Bonferroni correction was made for assessing the treatment effect at each time point. The difference and 95% confidence interval (CI) between medians were calculated with Hodges-Lehmann estimator. The relative risk (RR) and 95% CI were used to describe the differences in dichotomous outcomes. Data are analyzed using SPSS 25.0 (IBM Corp, Armonk NY) and hypothesis tests are two-sided at a level of 0.05.

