## J. Outcome measures

The primary outcome is the incidence of perioperative anxiety in patients from the day of surgery to 3 days after surgery after two sessions of tDCS intervention. Perioperative anxiety was measured using the Hospital Anxiety and Depression Scale-Anxiety (HADS-A) (**Appendix 1**). A HADS-A score of 8 or more is considered to be a patient experiencing anxiety. On the day before surgery, the researcher assesses the patient for anxiety in the ward treatment room (T0), followed by a second assessment of anxiety (T1) after the first tDCS intervention. On the day of surgery, the researcher conducted separate assessments before (T2) and after (T3) administering the second tDCS stimulus. Anxiety scores were assessed at two hours after surgery (T4), on the

---

first day after surgery (T5), the second day after surgery (T6), the third day after surgery (T7), and the third month after surgery (T8).

Secondary outcomes included anxiety scores (T1-T8), the incidence of postoperative delirium (POD, assessed by the Confusion Assessment Method [CAM] or Confusion Assessment Method intensive care unit [CAM-ICU] **[Appendix 2]** on the day of surgery and three days after surgery [T4-T7]); pain scores (assessed by the Numeric Rating Scale [NRS] **[Appendix 3]** at T4-T7); frail scores (assessed by the Fatigue, Resistance, Ambulation, Illness and Loss of Weight Index [FRAIL] **[Appendix 4]** at T5-T8); and sleep quality score (assessed by the Pittsburgh Sleep Quality Index [PSQI] **[Appendix 5]** at T4-T8).

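### No frailty score is scheduled at T0, so the baseline-adjusted model cannot be fitted for FRAIL as written, and two items that are in effect fixed over days 1-3 dilute three of its four visits

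*Protocol*

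**What the plan says.** Protocol, Methods, section G (Statistical Analysis): "The linear mixed-effects model is used to compare the secondary outcomes, with baseline (T0) values as covariates". Treatment, time and their interaction are fixed effects, with a random intercept per subject. No scored secondary outcome is exempted from the baseline term.

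Protocol, Methods, section J (Outcome measures): the secondary outcomes include "frail scores (assessed by the Fatigue, Resistance, Ambulation, Illness and Loss of Weight Index", to be assessed at T5 to T8. The same section defines T5, T6 and T7 as postoperative days 1, 2 and 3, and T8 as month 3. It describes one assessment at T0: "On the day before surgery, the researcher assesses the patient for anxiety in the ward treatment room (T0"). Pain is listed at T4-T7 and PSQI at T4-T8, also without T0.

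Protocol, Appendix 4 (FRAIL): five yes/no items, total 0 to 5, with 3 or more classed as frail. Two items look back or count history: "Have you lost more than 5% of your weight in the past year" and "Do you have more than 5 illnesses (confirm with doctor or medical records". The other three (fatigue, one flight of stairs, one block) state no recall period.

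**The concern.** The analysis section asks for a covariate that the visit schedule does not supply. This is a gap in data collection rather than a detail that can wait for a statistical analysis plan: if FRAIL is not scored before the first stimulation, it cannot be adjusted for later.

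The instrument makes the gap matter more. Part of the FRAIL total is patient history that will hardly move between days 1, 2 and 3. That part differs between patients for reasons unrelated to tDCS, and a T0 score would absorb most of it. Without T0 it stays in the error term at every visit. What is at stake is the precision of one secondary outcome and whether its stated model can be run at all.

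**Working it through.** The protocol gives no planning figure for FRAIL, so there is none to reproduce. The check sets the sections side by side and then sizes the loss under stated assumptions.

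**1. Is there a T0 value?**

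| Secondary score | Visits listed (section J) | T0 assessment described? |
|---|---|---|
| Anxiety (HADS-A) | T1-T8 | Yes, in a separate sentence |
| Pain (NRS) | T4-T7 | No |
| FRAIL | T5-T8 | No |
| PSQI | T4-T8 | No |

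Section G asks for T0 values. If that means each outcome's own baseline, the covariate exists for anxiety only.

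**2. How much of the FRAIL total can move over days 1-3?** Two of five items (illness count, past-year weight loss) are in effect fixed; three of five can change. With 0, 1 or 2 of the fixed items positive, the total can range over 0-3, 1-4 or 2-5. A patient can therefore move by up to 3 points, enough to go from robust (0) to frail (3). Three of the four FRAIL visits (T5, T6, T7) fall in this window. At T8 the one-year weight item still covers about 12 - 3 = 9 months before surgery.

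**3. What do the fixed items cost in power at one visit?** This is an illustration with assumed item rates, independent items and 88 patients per group (the evaluable number in section F). If each changeable item is positive in 60% of controls and 50% of treated patients, the mean difference is 3 × 0.10 = 0.30.

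- Three changeable items only: variance = (3 × 0.24 + 3 × 0.25)/2 = 0.735, SD 0.857. SE = 0.857 × √(2/88) = 0.129. Power = Φ(0.30/0.129 - 1.96) = 0.64.
- All five items, each fixed item positive in a share p: variance = 0.735 + 2p(1 - p). The difference stays 0.30.

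| Fall in each changeable item | Three items | Five, p = 5% | Five, p = 20% | Five, p = 40% |
|---|---|---|---|---|
| 60% to 50% | 0.64 | 0.59 | 0.49 | 0.44 |
| 60% to 40% | 0.997 | 0.993 | 0.974 | 0.953 |

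The fixed items add variance and leave the mean difference unchanged. The effect is diluted, not removed.

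**4. What would a T0 score recover at T8?** Adjusting a single follow-up score for baseline multiplies the residual variance by 1 - ρ², where ρ is the correlation between T0 and T8, and the standard error by √(1 - ρ²). The protocol gives no ρ, so a range is assumed.

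| ρ (assumed) | 1 - ρ² | SE ratio | SE reduction |
|---|---|---|---|
| 0.3 | 0.91 | 0.95 | about 5% |
| 0.6 | 0.64 | 0.80 | 20% |
| 0.8 | 0.36 | 0.60 | 40% |

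**The case against.** **The visit list may give outcome times only.** Anxiety is listed from T1 although it is measured at T0, so the absence of T0 from the FRAIL entry does not by itself prove that no baseline is taken. This is fair, but T0 anxiety has its own sentence in section J, and nothing in the protocol does the same for FRAIL.

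**The T0 covariate could mean T0 anxiety.** A model could then be fitted. That is not the natural reading, and it would leave prior frailty unadjusted.

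**Randomised groups can be compared without a baseline.** This stands. Allocation is 1:1, and both arms have the same type of surgery and the same anaesthesia protocol. A reader might infer that a FRAIL difference on days 1-3 would reflect earlier frailty or recovery from surgery rather than tDCS. The documents do not support that: surgical recovery is common to both arms, and baseline imbalance is chance that the test and interval already allow for.

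**T5-T7 still carry information.** This also stands. A reader might infer that three of the four visits cannot show a treatment effect. Three of the five items ask about present state and can change within days, so that inference is wrong. Nor is T8 simply lost in an average: section G tests the interaction first and goes to individual time points if it is significant. Only when it is not does the test move to the treatment main effect, where, with equal visit weights, T5-T7 make up three quarters.

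**The gap is not peculiar to FRAIL.** Correct. Pain and PSQI have it too, so the repair belongs in sections G and J, not in Appendix 4.

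**Conclusion.** The point holds as a minor one on a secondary outcome. Sections G and J do not fit together: a T0 covariate is specified, and no T0 FRAIL is scheduled. The model cannot be fitted for FRAIL as written, provided the covariate means the outcome's own baseline. Separately, two of five items are in effect fixed over days 1-3, which dilutes three of the four visits.

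The cost is lost precision, not bias. The counts (two of five items, three of four visits, no T0) come from the protocol. The standard-error reduction of about 5% to 40% at T8 rests on an assumed correlation of 0.3 to 0.8, and the power illustration on assumed item rates and independent items. Neither should be read as an estimate for this trial.

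**What to change.** - **Section J:** add one FRAIL assessment at T0, before the first stimulation.
- **Section G:** name that score as the FRAIL covariate, and report the T8 between-group difference adjusted for T0 as the main FRAIL comparison. T5-T7 may stay as descriptive data. Dropping them is a trade-off that the baseline gap does not require.
- **Pain and PSQI:** for each, either collect a T0 value or state that its model has no baseline covariate. If a T0 FRAIL can no longer be collected, say the same for FRAIL.

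The cost is one extra five-question form per patient on the day before surgery and a few words in two sections. The gain may be small if T0 and T8 correlate weakly.

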## Appendix 5. Pittsburgh Sleep Quality Index (PSQI)

---

### Pittsburgh Sleep Quality Index

---

Name:

Date:

Instructions:

The following questions relate to your usual sleep habits during the past month only. Your answers should indicate the most accurate reply for the majority of days and nights in the past month.

Please answer all questions.

1. During the past month, when have you usually gone to bed at night?

USUAL BEDTIME:

2. During the past month, how long (in minutes) has it usually taken you to fall asleep each night?

NUMBER OF MINUTES :

3. During the past month, when have you usually gotten up in the morning?

USUAL GETTING UP TIME :

4. During the past month, how many hours of actual sleep did you get at night?  
(This may be different than the number of hours you spend in bed.)

HOURS OF SLEEP PER NIGHT :

For each of the remaining questions, check the best response. Please answer all questions.

5. During the past month, how often have you had trouble sleeping because you...

- (a) Cannot get to sleep within 30 minutes

Not during past month

The Less than Once a week

Once or twice a week

Three or more times a week

- (b) Wake up in the middle of the night or early morning

Not during past month

The Less than Once a week

Once or twice a week

Three or more times a week

- (c) Have to get up to use the bathroom

Not during past month

The Less than Once a week

---

|                      |                            |
|----------------------|----------------------------|
| Once or twice a week | Three or more times a week |
|----------------------|----------------------------|

(d) Cannot breathe comfortably

|                       |                            |
|-----------------------|----------------------------|
| Not during past month | The Less than Once a week  |
| Once or twice a week  | Three or more times a week |

(e) Cough or snore loudly

|                       |                            |
|-----------------------|----------------------------|
| Not during past month | The Less than Once a week  |
| Once or twice a week  | Three or more times a week |

(f) Feel too cold

|                       |                            |
|-----------------------|----------------------------|
| Not during past month | The Less than Once a week  |
| Once or twice a week  | Three or more times a week |

(g) Feel too hot

|                       |                            |
|-----------------------|----------------------------|
| Not during past month | The Less than Once a week  |
| Once or twice a week  | Three or more times a week |

(h) Had bad dreams

|                       |                            |
|-----------------------|----------------------------|
| Not during past month | The Less than Once a week  |
| Once or twice a week  | Three or more times a week |

(i) Have pain

|                       |                            |
|-----------------------|----------------------------|
| Not during past month | The Less than Once a week  |
| Once or twice a week  | Three or more times a week |

(j) Other reason(s), please describe:

How often during the past month have you had trouble sleeping because of this?

|                       |                            |
|-----------------------|----------------------------|
| Not during past month | The Less than Once a week  |
| Once or twice a week  | Three or more times a week |

6. During the past month, how would you rate your sleep quality overall?

|           |             |            |          |
|-----------|-------------|------------|----------|
| Very good | Fairly good | Fairly bad | Very bad |
|-----------|-------------|------------|----------|

7. During the past month, how often have you taken medicine (prescribed or “over the counter”) to help you sleep?

|                       |                            |
|-----------------------|----------------------------|
| Not during past month | The Less than Once a week  |
| Once or twice a week  | Three or more times a week |

---

8. During the past month, how often have you had trouble staying awake while driving, eating meals, or engaging in social activity?

|                       |                            |
|-----------------------|----------------------------|
| Not during past month | The Less than Once a week  |
| Once or twice a week  | Three or more times a week |

9. During the past month, how much of a problem has it been for you to keep up enough enthusiasm to get things done?

|                            |                            |
|----------------------------|----------------------------|
| No problem at all          | Only a very slight problem |
| Only a very slight problem | A very big problem         |

10. Do you have a bed partner or roommate?

|                                        |                                |
|----------------------------------------|--------------------------------|
| No bed partner or roommate             | Partner/roommate in other room |
| Partner in same room, but not same bed | Partner in same bed            |

If you have a roommate or bed partner, ask him/her how often in the past month you have had...

(a) Loud snoring

|                       |                            |
|-----------------------|----------------------------|
| Not during past month | The Less than Once a week  |
| Once or twice a week  | Three or more times a week |

(b) Long pauses between breaths while asleep

|                       |                            |
|-----------------------|----------------------------|
| Not during past month | The Less than Once a week  |
| Once or twice a week  | Three or more times a week |

(c) Legs twitching or jerking while you sleep

|                       |                            |
|-----------------------|----------------------------|
| Not during past month | The Less than Once a week  |
| Once or twice a week  | Three or more times a week |

(d) Episodes of disorientation or confusion during sleep

|                       |                            |
|-----------------------|----------------------------|
| Not during past month | The Less than Once a week  |
| Once or twice a week  | Three or more times a week |

(e) Other restlessness while you sleep: please describe

|                       |                            |
|-----------------------|----------------------------|
| Not during past month | The Less than Once a week  |
| Once or twice a week  | Three or more times a week |

---
